## Abstract

**Background:**

It is becoming increasingly necessary for community health centers to make rehabilitation services available to patients with osteoarthritis of the knee. However, for a number of reasons, including a lack of expertise, the small size of community health centers and the availability of only simple medical equipment, conventional rehabilitation therapy has not been widely used in China. Consequently, most patients with knee osteoarthritis seek treatment in high-grade hospitals. However, many patients cannot manage the techniques that they were taught in the hospital. Methods such as acupuncture, *tuina*, Chinese medical herb fumigation-washing and t’ai chi are easy to do and have been reported to have curative effects in those with knee osteoarthritis. To date, there have been no randomized controlled trials validating comprehensive traditional Chinese medicine for the rehabilitation of knee osteoarthritis in a community health center. Furthermore, there is no standard rehabilitation protocol using traditional Chinese medicine for knee osteoarthritis. The aim of the current study is to develop a comprehensive rehabilitation protocol using traditional Chinese medicine for the management of knee osteoarthritis in a community health center.

**Method/design:**

This will be a randomized controlled clinical trial with blinded assessment. There will be a 4-week intervention utilizing rehabilitation protocols from traditional Chinese medicine and conventional therapy. Follow-up will be conducted for a period of 12 weeks. A total of 722 participants with knee osteoarthritis will be recruited. Participants will be randomly divided into two groups: experimental and control. Primary outcomes will include range of motion, girth measurement, the visual analogue scale, and results from the manual muscle, six-minute walking and stair-climbing tests. Secondary outcomes will include average daily consumption of pain medication, ability to perform daily tasks and health-related quality-of-life assessments. Other outcomes will include rate of adverse events and economic effects. Relative cost-effectiveness will be determined from health service usage and outcome data.

**Discussion:**

The primary aim of this trial is to develop a standard protocol for traditional Chinese medicine, which can be adopted by community health centers in China and worldwide, for the rehabilitation of patients with knee osteoarthritis.

**Trial registration:**

Clinical Trials Registration: ChiCTR-TRC-12002538

## Background

Knee osteoarthritis (KOA) increases in prevalence with age and causes pain, loss of functional independence and psychological impairment, and reduces the overall quality of life of affected individuals [1-3]. Based on epidemiological results, the incidence rate of osteoarthritis in the Chinese population is approximately 10% and the number of patients with KOA is greater than 50 million [4]. KOA has been identified as one of the most serious diseases that can affect an individual during his or her lifetime. It is a degenerative disorder caused by the interplay of genetic, metabolic, biochemical and biomechanical factors and results in pain, swelling and malformation of the knee joint [5]. KOA is prevalent and chronic and is associated with physical and psychological dysfunction. It reduces quality of life by inhibiting or preventing sufferers from carrying out activities such as walking, climbing stairs, doing housework, socializing and engaging in outdoor pursuits [6]. Furthermore, dysfunction due to KOA strongly influences employment status, productivity [7,8] and increases obesity rates [9], especially among older people. Pain, swelling, malformation and muscle weakness are often interrelated, leading to a downward cascade in physical as well as mental function [10-12].

During rehabilitation, patients with KOA require good pain control with few adverse events (AEs). Clinical guidelines advocate conservative non-drug strategies for the treatment of KOA [13], such as muscle-strengthening exercises, electromagnetic therapy and acupuncture. These conventional rehabilitation therapies are focused on controlling pain as well as reducing physical disability and impairment, while minimizing the potentially harmful side effects of medication [14]. These therapies can improve KOA patient outcomes [15], but are often only offered in high-grade hospitals and not in community health centers (CHCs). Consequently, the direct and indirect health-care costs associated with KOA frequently become a major burden to patients. After their discharge, patients will often abandon the rehabilitation therapy techniques they have learned and the KOA will become progressively worse. Therefore, as the patients aging and comorbidities increasing, a more convenient, effective, simple and inexpensive approach to rehabilitation is necessary for those with KOA.

The use of traditional Chinese medicine (TCM) for the treatment of KOA has increased substantially. In Chinese medicine, KOA is considered to originate in the tendons and bones, but manifests as viscera insufficiency and *biao* or *branch* excess. The invasion of evil pathogens, due to wind-cold-dampness, is linked to blood stasis, which then leads to *wei zheng* and *bi zheng*[16]. *Wei zheng* is treated by viscera reinforcement and *bi zheng* is treated by wind-cold-dampness purging and blood activation.

TCM has been used for health care in China for thousands of years. Some TCM rehabilitation methods, such as Chinese medical herbal patches, traditional exercises (developed from simplified t’ai chi and *yi jinjing*) and acupuncture have been reported to improve KOA in patients clinically [17-20]. The comprehensive TCM rehabilitation protocol (CTCMRP) comprises Chinese medical herb fumigation-washing (done to dispel wind-cold-dampness and to activate blood circulation in the knee), traditional exercise training, acupuncture and bloodletting via puncture. CTCMRP can enhance muscle strength, improve balance, reduce knee pain, stimulate the governor vessel and spine, and can regulate the function of the viscera, *qi* and blood in the *zang*-*fu* organs.

However, results from randomized controlled trials examining TCM treatments for KOA are contradictory and there is no standard rehabilitation protocol for KOA treatment using TCM (SRPTCM) [21]. Therefore, in the current study a protocol was designed in which KOA patients will be treated using CTCMRP in CHCs. The data from this study will shed light on the use of TCM for KOA rehabilitation.

## Methods/design

### Study design

This will be a cluster randomized controlled trial with blinded assessment (Figure 1). The trial will comprise a 4-week intervention, using the CTCMRP and conventional therapy (CT), and a 12-week follow-up period. The protocol will be conducted at CHCs run by the Affiliated People’s Hospital of Fujian University of Traditional Chinese Medicine (Fujian province, China), the Comprehensive Traditional and Western Medicine Hospital of Guangdong province (Guangdong province, China), the Chengdu Military Region General Hospital of the Chinese People’s Liberation Army (Sichuan province, China) and the First Affiliated Hospital of Guangzhou University of Traditional Chinese Medicine (Guangdong province, China). To include a broad range of patients, this protocol includes CHCs in different areas. Fujian University of Traditional Chinese Medicine (FJTCM) is responsible for training and supervising rehabilitation therapists at all clinical sites. The evidence-based medicine center, which will be used for documentation and data analysis, is an independent site that performs data monitoring, randomization and statistical evaluation and will be blind to the intervention. Patients will be recruited through CHC outpatient clinics. The Human Research Ethics Committee at Fujian University of Traditional Chinese Medicine (Fujian province, China) approved the study.

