### Randomization and allocation

Following an epidemiological survey, the CHC randomization list for this study will be computer generated using SAS software (Version 8.2, SAS Institute, Cary, NC, USA) and concealed at an independent evidence-based medical center. Employees at the medical center will also be blinded to the intervention. Treatment allocation will start when it has been determined that a study participant meets the inclusion criteria and has signed the informed consent.

The CHC randomization program will assign subjects to each group and each participant’s group number will be displayed (CTCMRP versus CT rehabilitation) on the back of the form. Baseline measurements will not be viewed until the end of the study to ensure blinded assessment. The allocation list will be protected and held by FJTCM. In the event of an emergency, the individual’s randomization code and group allocation can be identified. Therapists at each participating CHC will provide treatment, as usual, to patients who are not eligible or willing to participate.

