### Sample size

In cluster randomized trials, the inspection efficiency comes from the random unit number (cluster number) rather than the size. There are two important factors when estimating the sample number: (1) The number within each cluster group and (2) the intraclass correlation coefficient estimate. The total number of subjects (*n*) from all of the CHCs was calculated according to the estimation formula [23]:

$$n=\frac{{\left(\mu_{\alpha }+\mu_{\beta }\right)}^{2}\left[\pi_{1}\left(1-\pi_{1}\right)+\pi_{2}\left(1-\pi_{2}\right)\right]\left[1+\left(m-1\right)\rho \right]}{{\left(\pi_{1}-\pi_{2}\right)}^{2}}$$

In a trial test of this protocol, the curative effect rate after rehabilitation of KOA was 70% in the control group (*π*_1_) and 82.3% in the experimental group (*π*_2_); this will be used as the main index. The number of qualified participants recruited from each CHC (*m*) will not be less than 17. Prior data indicate that the intra-CHC correlation coefficient (*ρ*) is likely to be, at most, 0.020, and*μ*_*α*_ = 0.05 and *μ*_*β*_ = 0.10.

There are 38 CHCs. Based on the formula, each group (control and experimental) will comprise 323 participants. A total number of 722 subjects will be included to allow for a dropout rate of 10%.

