### Statistical analysis

Statistical analysis will be conducted using SAS software (version 8.2, SAS Institute, Cary, NC, USA). All tests will be two-tailed with *P* values of less than 0.05 considered statistically significant.

Descriptive statistics will be presented for each group as the mean ± standard deviation and all enumeration data will be presented as constituent ratio and rate in the outcomes from baseline to each time point. Changes in differences between groups in the primary and secondary outcomes, before and after treatment and during the follow-up period (at 4 weeks and 12 weeks), will be analyzed using repeated measures ANOVA or a rank-sum test.

Changes in effect sizes between pre- and post-intervention will be performed using the Wilcoxon test and chi square test. The effect size will be evaluated with safety set (SS), full analysis set (FAS), per-protocol set (PPS) and cost-effectiveness analysis. Demographic and CHC characteristics, as well as baseline data, will be analyzed using the FAS to assess the baseline and CHC comparability between groups. The primary analysis of the data will be undertaken using FAS with the principle of intention-to-treat and the PPS. The secondary analysis of the data will be undertaken using PPS. To account for missing data, multiple imputation of missing follow-up measures will be performed per the methods used for missing data [41]. The PPS will be used to assess adherence, the SS to assess adverse events and the cost-effectiveness analysis to assess health economics.

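### Centers are spread on purpose over four parent hospitals, but the described allocation and named tests make no use of hospital, giving up precision and protection against a lopsided draw

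*Protocol article*

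**What the plan says.** All places are in the protocol article.

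- **Study design:** "This will be a cluster randomized controlled trial with blinded assessment". The CHCs are run by four named hospitals: one in Fujian, two in Guangdong, one in Sichuan. The spread is deliberate: "To include a broad range of patients, this protocol includes CHCs in different areas".
- **Randomization and allocation:** "the CHC randomization list for this study will be computer generated using SAS software". The section covers how the list is concealed and who holds it. It names no stratum, block or pairing by hospital or province.
- **Sample size:** "There are 38 CHCs"; the number of qualified participants per CHC "will not be less than 17"; the intra-CHC correlation "is likely to be, at most, 0.020". No area component is named, and the number of CHCs per hospital is not given.
- **Statistical analysis:** changes in the primary and secondary outcomes "will be analyzed using repeated measures ANOVA or a rank-sum test". Wilcoxon and chi-square tests are named for the pre-post changes. The only stated use of site is a descriptive check "to assess the baseline and CHC comparability between groups".

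**The concern.** The design brings in a source of variation that is known for every CHC before allocation, and the article then describes no step that uses it. Parent hospital is a layer above the CHC. A model with a CHC effect alone would put area variation into the standard error, but would neither balance it nor take it out.

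Area differences in case mix or local practice would then add noise to the arm contrast. In the one allocation actually drawn, they could also move the estimate by an amount that depends on how evenly each hospital's CHCs happened to split. Checking comparability afterwards can show such a split but does not correct for it.

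**Working it through.** **1. The plan's own figure.** Inputs from Sample size: rates of 70% and 82.3%, m = 17, ρ = 0.020. I read the printed 0.05 and 0.10 as two-sided alpha (Statistical analysis states two-tailed tests) and beta.

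- Design effect = 1 + (17 − 1) × 0.020 = 1.32
- Variance sum = 0.70 × 0.30 + 0.823 × 0.177 = 0.2100 + 0.1457 = 0.3557
- n per group = (1.960 + 1.282)² × 0.3557 × 1.32 / 0.123² = 326

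The stated 323 (19 CHCs × 17) is within 1% of this. At 323 per group, SE = √(0.3557 × 1.32 / 323) = 0.0381, and power = Φ(0.123 / 0.0381 − 1.960) = 0.897.

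**2. How uneven an unrestricted draw can be.** The CHCs per hospital are not given, so two splits are assumed. Each was simulated with 38 CHCs allocated 19:19 at random without strata.

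| Assumed CHCs per hospital | Some hospital differs by 4 or more CHCs between arms | by 6 or more |
|---|---|---|
| 10/10/9/9 | about 53% | about 14% |
| 19/9/5/5 | about 31% | about 6% |

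In the first row, a difference of 4 or more means at least 7:3 in a hospital of 10, or 7:2 in a hospital of 9.

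**3. What that does to the arm difference.** The between-hospital variance is not given either. Let h be the part of the 0.020 that is due to hospital. The average binomial variance is 0.3557 / 2 = 0.178, so the hospital SD is √(h × 0.178). Four evenly spaced hospital rates with range r have variance 5r²/36, which gives r. The chance tilt is the arm difference produced by the hospital mix alone, simulated with the 10/10/9/9 split.

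**4. What removing it gains.** Balancing and adjusting for hospital leaves design effect = 1 + 16 × (0.020 − h), used in the power formula of step 1.

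| h (assumed) | Hospital SD, points | Range r, points | 95th percentile of chance tilt, points | Design effect after adjustment | Power at 323 per group |
|---|---|---|---|---|---|
| 0 | 0 | 0 | 0 | 1.32 | 0.897 |
| 0.005 | 3.0 | 8 | 1.8 | 1.24 | 0.914 |
| 0.010 | 4.2 | 11 | 2.6 | 1.16 | 0.931 |
| 0.015 | 5.2 | 14 | 3.2 | 1.08 | 0.946 |

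Against the planned 12.3 points, the tilt at the 95th percentile is 1.8/12.3 = 15% to 3.2/12.3 = 26% of the effect. The power figures presuppose an analysis that accounts for CHC.

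**The case against.** **The article is silent rather than wrong.** It does not say that the list is unrestricted, and strata and covariates are often left to the full protocol or analysis plan. This stands as far as it goes: a reader might infer that hospital is ignored throughout the trial, and the text does not establish that. But the article does commit to named tests. Three of them (rank-sum, Wilcoxon, chi-square) cannot take a hospital term in ordinary form, and repeated measures ANOVA is named without one. The point therefore rests on the analysis as written, not only on a missing detail.

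**Chance imbalance is not bias, and the sample size may already allow for it.** Both stand. Randomization without strata is unbiased over repeated draws. If the 0.020 includes area variation, the planned SE of 3.8 points contains it, and unadjusted power is 0.897 against a 90% target. The gain is then extra precision, not repair of a shortfall. The article does not say whether the prior data behind 0.020 spanned areas, so it gives no ground for claiming a shortfall.

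**Larger tilts are easy to produce by assumption.** A reader might suppose hospitals 20 points apart in response rate. That has variance 5 × 0.20² / 36 = 0.0056, or 0.0056 / 0.178 = 0.031 of correlation from hospital alone. This exceeds the stated total of at most 0.020, so it is not used here.

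**The plan has features that narrow area differences.** One university trains and supervises therapists at all sites, and outcomes are analyzed as change from baseline. These should reduce hospital differences, though they need not remove them, and they favor the lower rows of the table.

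**The allocation section also speaks of assigning subjects.** Individual allocation would make hospital imbalance much smaller. Study design and Sample size, however, both state cluster randomization, and the calculation follows them.

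**Conclusion.** The point holds as a cheap improvement in efficiency and balance. The CHCs are deliberately drawn from four parent hospitals, while the allocation as described and the tests as named make no use of that factor. It is not evidence of a biased comparison or of an underpowered trial.

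Its size rests on two things that the article does not give: the CHCs per hospital and the hospital share of the correlation. With 10/10/9/9 and no strata, about half of all draws leave some hospital split by 4 or more CHCs. With a hospital share of 0.005 to 0.015, the tilt at the 95th percentile is 1.8 to 3.2 points, and adjustment adds 1.7 to 4.9 percentage points of power. With no hospital differences the gain is nil.

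That the named tests also carry no CHC term is a separate and larger matter. This point does not depend on it, but the same model would settle both.

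**What to change.** **Statistical analysis.** Make the primary between-arm comparison a regression model that accounts for CHC (for example by a random effect) and includes parent hospital as a fixed effect with four levels. Use it in place of unadjusted rank-sum or chi-square tests: a linear model for continuous outcomes, a logistic one for the curative effect rate.

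**Randomization and allocation.** Stratify the list by parent hospital for any CHC not yet allocated. If it was already stratified, say so, name the factor and keep it in the model. State the number of CHCs per hospital and arm.

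**Cost.** No new data are needed, since each CHC's hospital is known. The hospital term uses 3 degrees of freedom: between-CHC degrees of freedom go from 38 − 2 = 36 to 33, which moves the two-sided 5% critical t only from 2.028 to 2.035. The real work is replacing the unadjusted tests with a model, which is more than adding one term. Recruitment began in October 2012 and is reported as ongoing, so stratification may have few CHCs left to act on. The model can still be fixed before outcomes are analyzed.

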**Figure 1 F1:**
[figure not shown]
Study flow chart.

### Participants

Patients suffering from pain, swelling, muscle weakness and stiffness of the knee will tested for KOA. All participants will be required to provide signed, informed consent prior to beginning baseline assessment and rehabilitation.

### Inclusion criteria

•Participants will have been diagnosed with KOA according to the criteria in the *Guide Diagnosis of Bone Arthritis* (2007) published by the Chinese Medical Association [22].

•Participants may be male or female and must be between 40 and 75 years of age.

•Participants will be considered to have early- to middle-stage KOA.

•Participants will understand the research and will have signed the informed consent.

•Symptoms will include pain, swelling, stiffness or malfunction of the knee according to the assessment scale.

### Exclusion criteria

Patients are excluded if they have:

•severe knee swelling

•a muscle strength of grade 2 or below according to a manual muscle test

•a history of trauma to the knees

•serious heart, kidney, liver or nervous system disease, or lower limb gangrene due to diabetes.

•lower limb dysfunction caused by spinal, hip or ankle joint disease, or prior knee joint surgery

•a tumor of the knee joint

•a cognitive or psychological disorder

•received traditional exercise training and/or *tuina* for the knee within the last 4 weeks

### Recruitment

Outpatients with KOA will be recruited from participating CHCs in China. All participants will be selected according to the above inclusion and exclusion criteria. Baseline measurements will include the general and demographic data for the subjects, assessment of the knee prior to testing, medication use, previous treatments, KOA complications and duration of KOA symptoms. Due to ethical considerations, non-steroidal, anti-inflammatory drugs will be permitted (and registered) as required for patients with visual analogue scale (VAS) scores over 5. All patients will be asked to refrain from seeking other forms of treatment during the trial. During the follow-up period, patients will be asked to report whether they have received other forms of treatment.

### Randomization and allocation

Following an epidemiological survey, the CHC randomization list for this study will be computer generated using SAS software (Version 8.2, SAS Institute, Cary, NC, USA) and concealed at an independent evidence-based medical center. Employees at the medical center will also be blinded to the intervention. Treatment allocation will start when it has been determined that a study participant meets the inclusion criteria and has signed the informed consent.

The CHC randomization program will assign subjects to each group and each participant’s group number will be displayed (CTCMRP versus CT rehabilitation) on the back of the form. Baseline measurements will not be viewed until the end of the study to ensure blinded assessment. The allocation list will be protected and held by FJTCM. In the event of an emergency, the individual’s randomization code and group allocation can be identified. Therapists at each participating CHC will provide treatment, as usual, to patients who are not eligible or willing to participate.

### Sample size

In cluster randomized trials, the inspection efficiency comes from the random unit number (cluster number) rather than the size. There are two important factors when estimating the sample number: (1) The number within each cluster group and (2) the intraclass correlation coefficient estimate. The total number of subjects (*n*) from all of the CHCs was calculated according to the estimation formula [23]:

$$n=\frac{{\left(\mu_{\alpha }+\mu_{\beta }\right)}^{2}\left[\pi_{1}\left(1-\pi_{1}\right)+\pi_{2}\left(1-\pi_{2}\right)\right]\left[1+\left(m-1\right)\rho \right]}{{\left(\pi_{1}-\pi_{2}\right)}^{2}}$$

In a trial test of this protocol, the curative effect rate after rehabilitation of KOA was 70% in the control group (*π*_1_) and 82.3% in the experimental group (*π*_2_); this will be used as the main index. The number of qualified participants recruited from each CHC (*m*) will not be less than 17. Prior data indicate that the intra-CHC correlation coefficient (*ρ*) is likely to be, at most, 0.020, and*μ*_*α*_ = 0.05 and *μ*_*β*_ = 0.10.

There are 38 CHCs. Based on the formula, each group (control and experimental) will comprise 323 participants. A total number of 722 subjects will be included to allow for a dropout rate of 10%.

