**Primary outcome measures**	
Pain	Visual analogue scale (VAS)
Swelling	Girth measurement
Knee range of motion	Range of motion (ROM)
Muscle strength	Manual muscle test (MMT)
Walking distance	Six-minute walking test (6 MW)
The time to ascend and descend a flight of stairs	Stair-climbing test (SCT)

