The stair-climbing test (SCT) is a physical performance test that measures the time it takes to ascend and descend a flight of stairs. Patients will be asked to complete the test as quickly as they can while still feeling safe and comfortable. Patients will be allowed to use a device if necessary, though participants will be encouraged to perform the test without the aid of a device if possible. Rejeski [34] found that a similar stair-climbing task had an excellent test–retest reliability coefficient of 0.93.

Based on the *Guidelines for the Clinical Research of Chinese Medicine New Drugs* (2002) [35], the curative effect for KOA is calculated as:

$$\begin{array}{l} \mathrm{Curative}\;\mathrm{effect}\\ \;=\left(\mathrm{Total}\;\mathrm{score}\;\mathrm{before}\;\mathrm{treatment}–\mathrm{Total}\;\mathrm{score}\;\mathrm{after}\;\mathrm{treatment}\right)\\ \;\times 100/\mathrm{Total}\;\mathrm{score}\;\mathrm{before}\;\mathrm{treatment} \end{array}$$

where the total score before and after treatment is based on the measures above.

The standard comprehensive effect:

•clinical cure: curative effect ≥ 90%

•obvious effects: 75% ≤ curative effect < 90%

•effective: 35% ≤ curative effect < 75%

•invalid: curative effect < 35%

The efficiency of a treatment is calculated as:

$$\begin{array}{l} \mathrm{Efficiency}\;\left(\%\right)=\left(\mathrm{Number}\;\mathrm{of}\;\mathrm{clinical}\;\mathrm{cures}\right)\\ \;+\mathrm{Number}\;\mathrm{of}\;\mathrm{cases}\;\mathrm{with}\;\mathrm{obvious}\;\mathrm{effects}\\ \;\left(+\mathrm{Number}\;\mathrm{of}\;\mathrm{effective}\;\mathrm{cures}\right)\\ \;\times 100/\mathrm{Total}\;\mathrm{number}\;\mathrm{of}\;\mathrm{cases} \end{array}$$

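### The protocol contradicts itself on which endpoint is primary: six unranked measures are listed, but the sample size rests on the curative effect rate, which neither list names

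*Protocol article*

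**What the plan says.** The protocol article speaks to the primary endpoint in five places.

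- **Abstract, Method/design:** "Primary outcomes will include range of motion, girth measurement, the visual analogue scale, and results from the manual muscle, six-minute walking and stair-climbing tests".
- **Outcome assessment, Table 6:** the same six measures stand under "Primary outcome measures". The curative effect rate has no row in any part of the table.
- **Sample size:** the calculation uses a binary endpoint. In a trial test of the protocol, "the curative effect rate after rehabilitation of KOA was 70% in the control group" and "82.3% in the experimental group", and "this will be used as the main index".
- **Primary outcomes:** after describing the six measures, the section defines the curative effect as a percentage change in a total score, sets response categories and gives a responder rate. On the score it says only "where the total score before and after treatment is based on the measures above".
- **Statistical analysis:** primary and secondary outcomes are compared between groups at 4 and 12 weeks. All tests are two-tailed, with P values "of less than 0.05 considered statistically significant". No outcome or visit is given precedence.

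**The concern.** A reader cannot tell from these sections whether the trial has one primary endpoint (the main index), six, or seven. The choice affects two things.

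- **Error rate.** With several unranked primaries, each judged at 0.05, a favourable result on one could be presented as a positive trial. The curative effect rate could likewise be promoted to the headline or dropped after the data are seen.
- **Power.** The number of participants was derived for one binary comparison. If the six listed measures are the primaries, the sample size says nothing about the trial's ability to detect an effect on any of them.

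**Working it through.** **1. Which endpoint the sample size belongs to.** Inputs from the Sample size section: π₁ = 0.70, π₂ = 0.823, ρ = 0.020, 38 centres, and m = 17 (recruits per centre "will not be less than 17"). The values 0.05 and 0.10 are printed as μ_α and μ_β. Put in literally they give n = 0.7, so they can only be error rates. With two-sided α = 0.05 and power 0.90 the normal quantiles are 1.960 and 1.282.

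- Variance term: 0.70 × 0.30 + 0.823 × 0.177 = 0.3557
- Squared difference: 0.123² = 0.01513
- Design effect: 1 + 16 × 0.020 = 1.32
- n per group = (1.960 + 1.282)² × 0.3557 / 0.01513 × 1.32 = 247.0 × 1.32 = 326

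The protocol states 323, which is also 19 × 17. For the total, 2 × 323 / 0.9 = 718, against 722 stated, which is 38 × 19. Both stated figures are reproduced closely, so the size is tied to the curative effect rate.

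**2. Power at the stated size.** The standard error is √(0.3557 × 1.32 / 323) = 0.0381, and 0.123 / 0.0381 = 3.226. Power = Φ(3.226 − 1.960) = 89.7%. No effect size or standard deviation is given for the six listed measures, so no such figure can be worked out for them.

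**3. Familywise error for six tests.** This takes one two-sided 0.05 test per outcome, all null hypotheses true, and success on any one counted as a positive trial. Independent tests give 1 − 0.95⁶ = 26.5%. The correlated cases were simulated with six equally correlated normal test statistics (400,000 draws). The correlations are assumptions, since the protocol gives none.

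| Assumed common correlation | Chance of at least one false positive |
|---|---|
| 0 | 26.5% |
| 0.3 | 24% |
| 0.5 | 21% |
| 0.7 | 16% |
| 0.9 | 11% |

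If the curative effect rate is a seventh primary, the independent case is 1 − 0.95⁷ = 30.2%.

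**4. What splitting alpha would cost.** As an illustration on the only comparison with stated inputs, Bonferroni over six gives α = 0.05 / 6 = 0.0083 (quantile 2.638). Power at 323 per group becomes Φ(3.226 − 2.638) = 72%. Restoring 90% would take about 477 per group, or 2 × 476.8 / 0.9 ≈ 1,060 in total.

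**The case against.** The strongest reply is that the protocol does name its deciding endpoint. The Sample size section calls the curative effect rate the main index, the Primary outcomes section defines it, and the six measures can be read as the components of its score. On that reading there is one primary endpoint, it is powered, and the abstract and Table 6 are merely incomplete. This stands in part. A reader of the abstract and Table 6 might infer that the sample-size endpoint lies wholly outside the primary outcomes, and the Primary outcomes section does not support that. But the same text does not say that the six measures give way to the rate, and two explicit lists call them primary.

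Other stronger readings also go beyond the documents:

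- **A claim of 90% power for the six measures.** No section makes it. The 90% is implied by the 0.10, and only for the curative effect rate.
- **Any one success makes a positive trial.** No section states this rule. None requires all six to succeed either, which would remove the inflation. The error figures are therefore conditional.
- **An error of 46% over two visits.** This is 1 − 0.95¹², which needs twelve independent tests. Visits in the same patients are correlated, and the repeated measures ANOVA that the protocol names may give one test per outcome.

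Finally, a multiplicity procedure is commonly left to the analysis plan, so its absence alone is no finding. What remains is what the article itself fixes: six primaries, one 0.05 threshold for all tests, and a main index missing from both lists.

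**Conclusion.** The inconsistency is real and needs correcting. The abstract and Table 6 disagree with the Sample size section about what is primary, the Primary outcomes section does not settle it, and no primary time point is named.

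If success on any one of the six would count, the familywise error is about 26.5% at most and about 24% to 11% over assumed common correlations of 0.3 to 0.9. Even the lowest of these is about twice the nominal 5%. The figures assume one test per outcome and individual tests that hold their 5% level.

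The implied power, 89.7% at 323 per group, holds for the curative effect rate only and depends on the 70% and 82.3% rates. For the six listed measures the power is unknown; the documents do not show that it is low.

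**What to change.** Name one primary endpoint and one time point, and use them consistently in the abstract, Sample size, Table 6, Primary outcomes and Statistical analysis.

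**Preferred.** Make the curative effect rate at the end of the 4-week treatment the single primary endpoint, and the six measures secondary. Two steps come with this:

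- Define the total score. The six measures have different units and improve in opposite directions: pain, girth and stair time fall, while range of motion, muscle grade and walking distance rise. The before-minus-after formula does not work on them as written.
- Confirm the 70% and 82.3% rates for the score so defined. They came from a trial test of the protocol and may not carry over to a repaired score, in which case the sample size must be checked again.

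**Alternative.** Keep the six as primary at a named time point, apply Holm across them, and state that the sample-size calculation covers only the curative effect rate.

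**Cost.** The preferred route keeps the full 0.05 for one test and is mainly a matter of wording, provided that the assumed rates hold for the defined score. Its downside is that fewer outcomes carry a primary claim. The alternative keeps the six claims but tests the smallest P value against 0.0083, with no stated power for any of them.
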